### 2.12. Quality Control of Study

#### 2.12.1. Research Process Management

The clinical supervisor will regularly inspect to ensure that the process of study is in accord with the protocol and standard practice and confirm that all the CRFs are filled correctly and completely and consistent with the original data. The researchers should record the contents accurately and carefully according to the requirements of CRFs. All the results in clinical trials should be verified to ensure that derive from original data.

#### 2.12.2. Measures for Consistency of Observation

Researchers in this trial will be trained based on a standardized operation practice (SOP) manual and possess the qualifications to carry it on. All research centers will establish uniform SOP and quality control sequence. If necessary, the research centers will hold interim meetings to check the preliminary work, summarize the problems, and propose the solution.

#### 2.12.3. Measures for Compliance of Participants

Researchers should distribute the research drugs to participants in time and supervise the use of drugs. Participants with poor compliance should strengthen the follow-up. Participants are required to bring the remaining drugs distributed last time in order to inspect the drug compliance.(1)$$\begin{array}{c} \text{Drug compliance}=\left[\frac{\left(\text{dispensing}-\text{remaining}\right)}{\text{dispensing}}\right]\times 100\%. \end{array}$$

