### 2.7. Study Visits and Data Collection

The study is divided into two periods, a 24-week drug intervention period and a 24-month follow-up period. After the intervention period commences, telephone visits will take place every 2 weeks and outpatient visits every 4 weeks. When the follow-up period commences, outpatient visits will take place every 6 months. An overview of data capture can be found listed in Table 1.

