### 2.11. Statistical Analysis

Three datasets will be used for statistical analysis, including a full-analysis set (FAS), per-protocol analysis set (PPS), and safety analysis set (SS). The FAS is the dataset composed of participants who have at least one postmedication evaluation data. The last observation carried forward (LOCF) method will be used for the missing data supplement. The PPS is the dataset composed of participants who meet the inclusion criteria, show good compliance, and complete the treatment plan. The SS is the dataset of all participants randomized to study, and safety record will be assessed, including adverse events and laboratory test results. All statistical tests are two-sided tests, and *P* < 0.05 will be considered statistically significant. Enumeration data will be expressed as frequency and analyzed using the chi-square test or Wilcoxon rank sum test. Measurement data will be described by means, standard deviation, maximum value, and minimum value and compared between groups using the group *t*-test, Fisher's exact test, or Wilcoxon rank sum test. Statistical analysis will be completed by the third-party statisticians.

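### The compliance rule is 80–120% of the amount prescribed, but the only formula divides by the amount dispensed and cannot exceed 100%

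*Protocol article*

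**What the plan says.** Three places in the protocol article bear on drug compliance.

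- Section 2.4.5 (Suspension Criteria) sets the only numerical threshold. A participant whose intake is under 80% or over 120% of the amount prescribed shows poor compliance and meets a suspension criterion.
- Section 2.12.3 (Measures for Compliance of Participants) gives the only measure. "Participants are required to bring the remaining drugs distributed last time in order to inspect the drug compliance". Compliance is then the amount dispensed minus the amount remaining, divided by the amount dispensed, times 100%.
- Section 2.11 (Statistical Analysis) makes compliance a condition of the per-protocol set (PPS), which holds "participants who meet the inclusion criteria, show good compliance, and complete the treatment plan". It gives neither a threshold nor a formula.

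On timing, section 2.7 says that during the intervention period "telephone visits will take place every 2 weeks and outpatient visits every 4 weeks", so drug can be counted about every 28 days. No section says how much drug is handed out per visit, or that it equals the amount prescribed.

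**The concern.** The rule and the measure use different denominators. The rule compares intake with what was prescribed; the formula compares it with what was handed over. The rule also has an upper limit above 100%, which the formula cannot reach.

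Two things are at stake. First, half of the rule cannot operate through the stated measure. Second, where the supply differs from the amount due between two visits, the 80% limit is in effect applied at some other level of true intake. That could change who is suspended for poor compliance and, if the same measure is used there, who enters the PPS. The control group takes no study drug, so any such error falls on the TCPM arm alone.

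**Working it through.** The plan states no numerical result that rests on this formula, so there is no figure to reproduce. The check is algebra on the formula itself.

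**Notation.** P = amount prescribed for the interval, D = amount dispensed, R = amount remaining, T = D − R = amount taken. Let k = D/P and t = T/P. The rule in section 2.4.5 concerns t, with limits 0.80 and 1.20. The value of k is not in the document; I assume 1.0 to 1.5.

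**Step 1: the ceiling (no assumption needed).** The formula is (D − R)/D. Since R cannot be negative, its maximum is D/D = 100%, reached when nothing is returned. It cannot pass 120% at any k.

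**Step 2: what the formula measures.** (D − R)/D = T/D = (tP)/(kP) = t/k. It equals t only when k = 1. A score of 80% therefore corresponds to a true intake of 80k% of the prescribed amount.

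**Step 3: values over the assumed range.** For a 28-day interval the supply is 28k days.

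| k | Days supplied | True intake needed to score 80% | Score at 90% intake | Score at 100% intake | Score at 130% intake |
|---|---|---|---|---|---|
| 1.0 | 28 | 80% | 90.0% | 100% | not possible |
| 1.1 | 30.8 | 88% | 81.8% | 90.9% | not possible |
| 1.2 | 33.6 | 96% | 75.0% | 83.3% | not possible |
| 1.25 | 35 | 100% | 72.0% | 80.0% | not possible |
| 1.3 | 36.4 | 104% | 69.2% | 76.9% | 100% |
| 1.5 | 42 | 120% | 60.0% | 66.7% | 86.7% |

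*Not possible* means that the supply does not contain that much drug.

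- At k = 1.0 the formula and the rule agree at the lower limit.
- At k = 1.2, 90% intake is inside the rule but scores 75.0% and fails.
- A perfect taker fails only if 1/k < 0.80, that is k > 1.25, or more than 35 days of drug for 28. At exactly 35 days the score is 80.0% and passes.
- Intake above 120% is possible only if k > 1.2. Over the rest of the assumed range (k up to 1.5) it always scores above 1.2/1.5 = 80% and passes.

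**Step 4: visit timing.** Even with exactly 28 days supplied, D equals the amount due only if the visit falls on day 28. Illustrations with assumed visit days:

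- Day 22, perfect intake: the formula gives 22/28 = 78.6% and fails; true intake is 100%.
- Day 21, supply used up: the formula gives 100%; true intake is 28/21 = 133%.
- Day 40, supply used up: the formula gives 100%; true intake is 28/40 = 70%.

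**The case against.** The strongest reply is that the misclassification has to be assumed. Nothing says that surplus is dispensed. If exactly the amount due is handed out and visits are punctual, formula and rule agree at 80%, and nobody can take 120% from trial supply, so the upper limit is idle rather than misapplied. To fail a perfect taker on a punctual visit needs a surplus above 25%. This stands, and it is why the consequences are stated conditionally. It does not remove the mismatch of denominators or the 100% ceiling.

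A reader might infer that over-use is undetectable in this trial. The document does not support that. Section 2.12.3 also says "Researchers should distribute the research drugs to participants in time and supervise the use of drugs", there are telephone contacts every 2 weeks, Table 1 has a TCPM record at each treatment visit, and supply counts could be set against the regimens in section 2.5.2. The limitation is in the formula; the article specifies no other calculation.

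A reader might also infer that the formula decides the PPS and biases its comparison. Section 2.4.5 does not cite the formula, section 2.11 gives no definition of compliance, and the consequence named in section 2.12.3 is closer follow-up. A fuller definition may exist in a document not shown. Moreover, any drug-count criterion can apply only to the TCPM arm, so that asymmetry would remain under a corrected formula.

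**Conclusion.** The contradiction is real and needs no assumption: sections 2.4.5 and 2.12.3 use different denominators, and the formula's maximum of 100% means it can never register the 120% limit.

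The lower-limit error is conditional. It is nil at k = 1.0 on a punctual visit. It grows with k: the effective limit is 88% of the prescribed amount at k = 1.1 and 120% at k = 1.5. These sizes rest on the assumed range of k, and the visit-timing examples on assumed visit days. The document supports no estimate of how many participants would be affected and no claim of a demonstrated bias in any result.

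The reach is limited to compliance-based suspension and, if the same measure is taken to define compliance there, PPS membership in the TCPM arm. Membership of the full-analysis set depends on having a post-medication evaluation, not on compliance.

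**What to change.** Reconcile sections 2.4.5 and 2.12.3 so that rule and formula share one denominator. One way that leaves the 80–120% limits unchanged is:

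compliance = (dispensed − returned) / (amount prescribed for the actual interval between visits) × 100%, cumulated over visits.

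This returns t directly. In the examples above it gives 90% instead of 75.0% (k = 1.2), 130% instead of 86.7% (k = 1.5), and 100%, 133% and 70% for the day-22, day-21 and day-40 visits.

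State in section 2.11 that this measure, with the same limits, is the one used for the PPS. Note also that the upper limit can be registered only when the supply dispensed exceeds the amount due for the interval. With k = 1 and a punctual visit, the revised formula also stops at 100%.

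The cost is one changed denominator and two clarifying sentences. Dispensed and returned counts are already collected, and the amount due follows from the stated regimens and the visit dates, so no new data are needed.

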## 3. Discussion

In the present clinical practice in China, prevention of T2DM mainly depends on the improvements in unhealthy lifestyles, which is hard to persist in. Several large-scale trials have demonstrated that use of some hypoglycemic drugs can decrease the incidence of diabetes to various degrees in those with prediabetes [12–15], though none are approved by the U.S. Food and Drug Administration, specifically for diabetes prevention. The cost, adverse reactions, tolerance, and other factors are also needed to be considered [4, 16]. TCM may hold a promise in the prevention of T2DM because of its characteristics of “treat disease before it arises,” which include strengthening the body constitution and regulating the high-risk factors leading to diabetes; in addition, TCM could also control the development of T2DM. This cognition corresponds with the thought of the prevention of T2DM. Prediabetes may fall under the TCM patterns of “spleen pyretic abundance,” etc. [17]. The main pathogenesis lies in spleen and stomach congestion, dampness-heat accumulation in the spleen, spleen deficiency and phlegm obstruction, liver depression and qi stagnation, and qi-yin dual insufficiency [9, 10]. In China, many prediabetic patients are more likely to choose the complementary TCPMs. Postmarketing TCPMs possess steady drug composition and defined dosage, which is convenient to observe the efficacy. In recent years, some randomized controlled trials (RCTs) have proved that TCPMs alone or TCPMs combined with lifestyle modification could be an effective intervention for the preventative treatment of T2DM [18–20]. Now, we aim to implement a clinical trial to observe the efficacy of TCPMs in the prevention of T2DM in Chinese subjects. The strength of our trial is that the trial design is a prospective cohort study, not an RCT, and the choice of intervention drugs in our trials is based on syndrome differentiation and treatment, which are more in accord with the clinical practice of TCM. The treatment duration is 6 months, and follow-up is continued for another two years, which is to observe the short-term and long-term effects of TCPMs. As to outcome assessment, we emphasize for incident diabetes and normalization of blood glucose, improvement of symptoms is also important for prediabetic patients to increase the quality of life.

We hypothesize that the prediabetic patients will benefit from TCPMs. If successful, this trial may provide comprehensive intervention plans that choose suitable TCPMs for diabetes prevention according to syndrome differentiation. Although clinical trials are strictly designed, there might also be potential limitations. Firstly, there is no placebo in the control group. Secondly, the long treatment and follow-up period may lead to poor patient compliance, which might greatly influence the therapeutic effect. More effort should be made to find a solution in future trials.

## Figures and Tables

**Figure 1 fig1:**
[figure not shown]
Flow diagram of enrollment, intervention, and assessments.

**Table 1 tab1:** Schedule of enrollment, allocation, visits, and assessments.

Time of visits	Enrolment	Allocation	Drug intervention period				Follow-up period			
	−2w	0w	4w, 8w	12w	16w, 20w	24w	12 m	18 m	24 m	30 m
*Collect basic medical history*										
Sign informed consent form	√									
Determine inclusion and exclusion criteria	√	√								
Determine withdrawal criteria	√	√	√	√	√	√	√	√	√	√
Fill in general information	√	√								
History of prediabetes and treatment	√									
Comorbidity and symptom	√									
Physical examination and consultation	√	√	√	√	√	√	√	√	√	√
Concomitant medication	√	√	√	√	√	√	√	√	√	√

*Efficacy assessment*										
Glycosylated hemoglobin		√		√		√	√	√	√	√
Fasting plasma glucose		√	√	√	√	√	√	√	√	√
2-hour postprandial blood glucose		√	√	√	√	√	√	√	√	√
Blood lipids		√		√		√	√	√	√	√
Carotic artery intima-media thickness		√		√		√	√	√	√	√
BMI, waist perimeter and hip perimeter, waist-hip ratio, and blood pressure		√	√	√	√	√	√	√	√	√
TCM symptom score		√		√		√	√	√	√	√

*Safety assessment*										
Vital signs		√				√	√	√	√	√
Routine blood, urine, and stool examination		√				√	√	√	√	√
Liver function		√				√	√	√	√	√
Renal function		√				√	√	√	√	√
Electrocardiogram		√				√	√	√	√	√
Hypoglycemic episodes			√	√	√	√	√	√	√	√
Adverse events			√	√	√	√	√	√	√	√

*Other work*										
Record of TCPMs		√	√	√	√	√	√	√	√	√
Research summary						√				√

## Data Availability

Once the main findings of the project are published, the trial steering committee will review all requests for data before access is granted. If appropriate, the anonymized data and associated documentation will be made available to users under a data-sharing agreement.
